### 2.10. Training

To increase compliance with the protocols in place, the healthcare professionals in the Clinical Care Group will undergo accredited training, which will cover the information related to assessment and data collection in both study groups, as well as the implementation of the health education intervention in the intervention group. The professionals assigned to the intervention group will be trained separately in order to avoid compromising the indications given to the other arm of this study.

### 2.11. Study Variables

For further information, see Supplementary File S1. Description of assessment tools.

#### 2.11.1. Primary Outcome Variable

The seven-item short FES-I scale (Spanish adaptation) scores will be collected at baseline, one month, six months, and one year after the health education intervention. The scale is validated for use with Spanish speakers, with a range of 7–28. A score equal to or greater than 11 is considered positive for FOF (see Table 1). The short FES-I scale showed a Cronbach’s alpha of 0.88 compared to the long version. In addition, the short FES-I obtained a Spearman’s rho correlation coefficient of 0.99 between T1 (measurement at baseline) and T2 (measurement at one month), as well as an intraclass correlation coefficient of 0.77 between T1 and T2 [32].

#### 2.11.2. Secondary Outcome Variable

Data on the incidence of falls at one month, six months, and one year after the health education intervention will be collected.

#### 2.11.3. Explanatory Variables

Sociodemographic variables: sex, age, marital status, number of cohabiting individuals, level of education, personal net monthly income, current or previous occupation, availability and type of support at home, perceived ability to receive family support, neighborhood, basic healthcare district, the Medea index (used to measure social inequalities in Spain), time spent in the neighborhood in years, housing characteristics, most frequent type of housing in the neighborhood, accessibility to basic services, perceived safety and walkability of the neighborhood.Functional variables: the Downton scale, the Barthel index, the SPPB scale total score, four-meter gait disturbance, balance disturbance, loss of lower limb strength, the Lawton-Brody index, physical activity recommended for this age group by the Spanish Ministry of Health (i.e., 150 min of moderate physical activity or 75 min of vigorous physical activity; balance exercises; muscle strengthening exercises; flexibility exercises). Data on this variable will be collected separately, and patients will be considered as meeting the recommended physical activity level, provided that 75% of the activities are carried out. This will include a variable regarding how many dimensions (from one to four) are met by the patient.Clinical variables: falls in the previous year (pre intervention); falls during intervention; fall-associated injuries (pre intervention, during intervention, and post intervention); mild visual problems or use of glasses; mild hypoacusis, either unilateral or corrected with a hearing aid; use of a walking device; pain (using a verbal numerical scale); anxiety (via the Generalized Anxiety Disorder-7 (GAD-7) questionnaire); depression (via the Patient Health Questionnaire-8 (PHQ-8); ability to practice self-care (via the Appraisal of Self-Care Agency Scale-Revised (ASA-R)); cognitive level (using the Mini-Mental State Examination); perceived health status; body mass index; urinary incontinence, comorbidities (using the Charlson index); medication; polypharmacy; high blood pressure; nursing diagnosis of risk of falling.Usual footwear variables: heel height in centimeters, type of sole, sole material, type of fastening.Feasibility and acceptability variables:○Feasibility (to be measured among professionals): recruitment rate, randomization, adherence to the health education intervention, follow-ups performed, safety/adverse events, difficulties in implementing the health education intervention. To be assessed at the end of the clinical trial.○Acceptability (to be assessed in patients assigned to the intervention group):-Participants: at the end of the health education intervention, data on its utility, usability, satisfactoriness, recommendability, as well as other open questions will be collected.-Professionals: data on the utility, usability, and satisfactoriness of the program, as well as their readiness to repeat it and other open questions will be collected.

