### 4.1. Intervention Group Arm

The health education intervention will consist of five initial group sessions, plus a reinforcement session after six months. The sessions will be two hours long and will preferably be held once per week. Each group will have approximately 15 participants. The contents detailed in Supplementary File S2. Educational program for nurses in the intervention group will be addressed.

The sessions will include nursing interventions aimed at improving participants’ knowledge, skills, and attitudes regarding their functional ability, fall prevention measures, anxiety management, and ability to cope with FOF and falls.

The activities to be performed during the intervention were drawn from standardized nursing interventions listed in the Nursing Interventions Classification (NIC) following a review of effective interventions addressing these issues [3,4,9,18,33]:NIC 1665. Functional ability enhancement.NIC 5612. Teaching: prescribed exercise.NIC 6490. Fall prevention.NIC 6486. Environmental management: safety.NIC 4700. Cognitive restructuring.NIC 5820. Anxiety reduction.NIC 5230. Coping enhancement.

To monitor the degree of compliance with the interventions as instructed in the protocol, ad hoc questionnaires will be sent after each session to all the professionals and patients who carry out the intervention in order to assess acceptability, feasibility, and satisfaction.

Health education workshops are a fundamental tool for teaching health education in the primary care setting. This workshop was designed following the methodology recommended by the Madrid Primary Care Management Board and is being reviewed by the Validation Commission for Educational Projects of the Community of Madrid (COVAM) for its free distribution throughout the Autonomous Community of Madrid.

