### 4.4. Data Analysis

A descriptive analysis by groups (intervention and control) of participants’ sociodemographic, functional, and clinical characteristics will be carried out to identify potential differences between the two study groups, with quantitative variables expressed as either means and standard deviations or medians and interquartile ranges depending on the normality or skewness of data distribution. Qualitative variables will be summarized as frequencies and percentages. Data on the effect of the health education intervention will be analyzed in both the intention-to-treat population and the per-protocol population. In the former case, all participants will be included and will be analyzed as part of the group to which their PCF will be randomly assigned. Should the percentage of missing data be higher than 5%, multiple imputation techniques will be used. In the per-protocol analysis, complete cases of patients will be included provided they have maintained adherence. The intervention group is required to be adherent and have at least 80% attendance at the initial five sessions. Safety, acceptability, and feasibility of the health education intervention will also be assessed.

The primary efficacy analysis, (FOF), will be the comparison between intervention and control groups fitting a fixed-effects ANOVA model. Model will include group and facility as independent variables, with facility being a nested factor within group. The short FES-I scale mean scores and their 95% confidence intervals will be provided for each facility, or by groups if no differences between facilities are observed. The effectiveness of the health education intervention in relation to fear of falling will be measured through the decrease in the short FES-I scale scores, assessed at three times: at 1-, 6- and 12 months after the intervention. The difference in means between the intervention and control groups will be analyzed. In addition, the variable will be examined dichotomously, using a cut-off point on the short FES-I scale of 11 or more to identify the presence of fear of falling. Multivariate models will be fitted to identify factors potentially related to FOF.

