For the secondary outcome variable (incidence of falls), a process similar to the main analysis will be followed, but this time fitting a fixed-effects logistic regression model, again nesting each facility within its group. The effectiveness of the health education intervention for the incidence of falls will be measured through the recording of falls (recorded in the medical history or reported by the patient), at 1-, 6- and 12-months post intervention. Both groups will be compared in terms of odds ratios, and their corresponding 95% confidence intervals will be provided.

To assess the impact of the health education intervention by time, mixed effects models will be adjusted, including time also as an independent variable and random intercepts for participants.

Data will be recorded in a paper data collection notebook and entered into an Excel spreadsheet by a single researcher in order to minimize the risk of transcription errors. The collected data will then undergo a second review to correct transcription errors, if necessary. Access to these data will be limited to authors until open access dissemination, after which they can be included on ClinicalTrials.gov.

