### 4.6. Clinical Risk Management

Clinical risk management has been considered to ensure the safety of participants in all phases of this study. Health education interventions to reduce fear of falling in older people at the community level have shown positive results in various studies [16,17,18,19,20,21,22,23,24]. For this study, those with evidence support have been selected, which is a guarantee of quality.

To ensure that no subjects with unfavorable conditions participate in this type of intervention at the community level and that no situations arise that create a risk to the health of the participants, measures will be taken at different stages of this study [37]:-Screening and pre-selection visits will allow the assessment of the baseline physical and mental condition of the participants, which will ensure whether they can safely participate in the multicomponent exercise program. Inclusion criteria include that participants must be independent for activities of daily living or with mild functional dependence, independent for walking, and not present cognitive impairment (details are given in the inclusion and exclusion criteria section).-The intervention visit will be carried out by nurses specifically trained in the field of primary care to implement the program, who will monitor the performance of the activities and ensure their adaptation to the functional capacities of each individual. Homogeneous training of the professionals involved in this study will ensure the safe implementation of the intervention.-Follow-up visits will allow close monitoring of each participant to monitor and detect possible conditions that pose a risk to health.-If during the intervention/follow-up a change in the patient’s clinical condition is detected that is a criterion for withdrawal, to ensure patient safety, the patient will not continue in this study. In addition, the patient will be followed up either in primary care or, if necessary, in specialized care.

In addition, this study has been approved by the Ethics Committee of the Gregorio Marañón Hospital and the Central Research Committee of the Primary Care Management of Madrid that guarantee the application of good research practices in the field of primary care. This study is considered a low-intervention clinical trial, in which the additional burden on the safety of the subjects is minimal compared to that of normal clinical practice and does not require coverage by an insurance contract [38].

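### Adverse events other than falls, and fall-associated injuries after baseline, are not collected per participant at any scheduled visit, which does not match the promised safety assessment

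*Protocol article*

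**What the plan says.** All places are in the protocol article.

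- **Source and timing.** Section 2.11.3 puts adverse events in a list of operational items: "Feasibility (to be measured among professionals): recruitment rate, randomization, adherence to the health education intervention, follow-ups performed, safety/adverse events". The end of that list sets the time of assessment at the close of the trial: "safety/adverse events, difficulties in implementing the health education intervention. To be assessed at the end of the clinical trial".
- **Fall-related harms.** The same section lists, among the clinical variables, "falls during intervention; fall-associated injuries (pre intervention, during intervention, and post intervention".
- **Visit schedule.** Table 2 marks post-intervention falls at baseline and at all three follow-up visits. It marks falls during the intervention at the post-initial visit and the booster. The clinical-variables row is marked at baseline only. No row is labelled adverse events or fall-associated injuries.
- **Analysis.** Section 4.4 states "Safety, acceptability, and feasibility of the health education intervention will also be assessed" and gives no data source for the safety part. For falls it is specific: effectiveness "will be measured through the recording of falls (recorded in the medical history or reported by the patient), at 1-, 6- and 12-months post intervention", and "Both groups will be compared in terms of odds ratios, and their corresponding 95% confidence intervals will be provided".
- **Monitoring.** Section 4.6 states "Follow-up visits will allow close monitoring of each participant to monitor and detect possible conditions that pose a risk to health".
- **Session feedback.** Under section 4.1, "ad hoc questionnaires will be sent after each session to all the professionals and patients who carry out the intervention", on acceptability, feasibility and satisfaction.

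**The concern.** The intervention includes a multicomponent exercise programme for people over 65 who fear falling. The exclusion criteria in section 2.6.2 themselves name conditions that make such exercise unsuitable, so the sponsor accepts that it carries some risk. Yet the only place where the article says how adverse events are obtained treats them as an implementation matter, alongside recruitment rate and practical difficulties, rather than as something recorded for each participant.

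At stake is what the trial can say about harm. Section 6 would recommend wide integration into routine practice if the intervention succeeds. That recommendation needs a safety statement covering more than falls, and such a statement needs events collected in the same way in both arms. Musculoskeletal pain, an exercise injury without a fall, or a faint has no stated place to be recorded at a visit.

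**Working it through.** No figure in the protocol bears on this point, so the check sets the sections side by side.

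**Step 1. Trace each kind of harm through the article.**

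| Harm | Where listed | Marked in Table 2 after baseline | Arm comparison stated |
|---|---|---|---|
| Post-intervention falls | 2.11.2 | Post-initial, 6-month and 12-month visits | Yes, odds ratio with 95% CI (4.4) |
| Falls during the intervention | 2.11.3, clinical | Post-initial visit and booster | None separately |
| Fall-associated injuries | 2.11.3, clinical, including during and after the intervention | None | None |
| Pain | 2.11.3, clinical | None | None |
| Adverse events | 2.11.3, feasibility, from professionals, end of trial | None | None; 4.4 only says that safety will be assessed |

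For an adverse-event row the count is 0 of 3 follow-up visits and 0 of 6 sessions (5 initial + 1 booster). With 150 participants, up to 3 × 150 = 450 planned participant-visits carry no such item.

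**Step 2. Ask whether Table 2 is merely condensed.** Section 2.11.3 also lists self-care ability, anxiety, perceived health and falls during the intervention as clinical variables. Table 2 gives each of these its own row or a shared one, with marks after baseline. So the table does separate out the clinical variables that are repeated. Pain and fall-associated injuries are left in the general row, marked at baseline only. For injuries this contradicts section 2.11.3, because injuries during and after the intervention cannot be recorded at baseline.

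**Step 3. Compare with the promises.** Section 4.6 says that follow-up visits detect health risks, but Table 2 schedules no adverse-event item in which a detected event would be entered. Section 4.4 promises a safety assessment, but for events other than falls the only stated input is the professionals' item in section 2.11.3.

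**Step 4. Check the session questionnaires as a substitute.** Feasibility is one of their topics and is also the heading under which adverse events appear, so they might capture events. But only the intervention arm has sessions. Events found that way would have no control-arm counterpart, and a comparison would partly measure how often each arm was asked.

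**Step 5. What proper collection would buy.** If an arm of n participants were fully observed with no event of a given kind, the one-sided 95% upper limit for its risk would be 1 − 0.05^(1/n), ignoring clustering:

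- n = 75 (recruited per arm): 1 − 0.05^(1/75) = 3.9%.
- n = 60 (120/2, after the allowed loss): 1 − 0.05^(1/60) = 4.9%.

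These limits are modest, and they hold only if each participant was actually asked. Without visit-level collection, an absence of reports does not support even this much.

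**The case against.** The strongest reply has four parts.

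1. **Falls are covered.** They are the most obvious harm here, they are recorded at follow-up from the medical history or the patient, and they are compared by arm. This stands. A reader might infer that the arms cannot be compared on safety at all; section 4.4 contradicts that. Nor is the feasibility item confined to one arm: section 2.11.3 limits only acceptability to the intervention group, and control-facility nurses are study professionals too.
2. **Individuals are protected during the trial.** A reader might infer that nothing could prompt action before the end. Sections 2.6.3 and 4.6 contradict that: nurses monitor the activities, and a change that meets a withdrawal criterion leads to withdrawal and clinical follow-up. This stands. What is missing is scheduled recording of non-fall events, not individual care.
3. **Assessed at the end may mean summarised at the end.** Adherence is in the same list and depends on session attendance, which must be noted as sessions occur. A reader might add five weekly sessions (about 4 weeks), 6 months to the pre-booster visit and 6 months after the booster, and conclude that staff must recall events over 12 to 13 months. The article mentions no recall, so that conclusion is not supported. Equally, it describes no running record of non-fall events to summarise.
4. **An article condenses.** Event forms may be in the full protocol or the data collection notebook, which are not shown. This answers an omission. It does not answer a source and time that are stated in print, or injuries listed for periods in which Table 2 does not collect them.

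**Conclusion.** The point holds in limited form. For harms other than falls, the article states an end-of-trial item obtained from professionals and schedules no participant-level collection: 0 of 3 follow-up visits and 0 of 6 sessions. Fall-associated injuries are listed during and after the intervention but have no follow-up row. Neither fits the safety assessment in section 4.4 or the monitoring in section 4.6, and non-fall harms could not be reliably compared between arms.

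The fear-of-falling and falls analyses are unaffected. The conclusion assumes that Table 2 is a complete list of what is collected at visits. If the data collection notebook already holds an adverse-event and injury item asked in both arms, what remains is to correct section 2.11.3 and Table 2 to say so.

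**What to change.** - **Section 2.11.3:** take safety/adverse events out of the professionals' end-of-trial feasibility item and define them as a participant-level variable.
- **Table 2:** add a row for adverse events and fall-associated injuries, marked at the post-initial, 6-month and 12-month visits, with the same question put to every participant in both arms.
- **Section 4.4:** state that these visit data are reported by randomised arm. Events seen at the five sessions and the booster are recorded separately and described for the intervention arm only, so that the extra contact does not distort the comparison.
- **Section 4.6:** refer to the new row as the place where findings at follow-up visits are recorded, so that sections 2.11.3, 4.4, 4.6 and Table 2 agree.

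The cost is one added item in the data collection notebook and a few minutes at visits planned at about 25, 45 and 20 minutes. No new visits or staff are needed, since a second nurse already observes each session (section 2.5). The downside is slightly longer visits and a higher count of reported events, in both arms.

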
## 3. Materials and Equipment

To carry out the health education intervention, at least two trained professionals per center are required, as well as a room with sufficient space and materials for participants to carry out the multicomponent exercise program explained in Supplementary File S2. Educational program for nurses in the intervention group.

## 4. Detailed Procedure

This study has two arms, an intervention and a control arm. Participants from PCFs assigned to the intervention arm would receive the group educational intervention, while participants from PCFs in the control group would receive care as usual. Participants will be assessed for eligibility based on the inclusion and exclusion criteria at the nurses’ office. In cases where the patient agrees to participate and meets the criteria, a screening visit will be conducted to confirm compliance. Screening sheets will be kept for those participants who do not meet the criteria or do not wish to participate.

Patients will be followed up for 12 months. Data collection visits will take place at baseline, one month, six months, and 12 months.

### 4.1. Intervention Group Arm

The health education intervention will consist of five initial group sessions, plus a reinforcement session after six months. The sessions will be two hours long and will preferably be held once per week. Each group will have approximately 15 participants. The contents detailed in Supplementary File S2. Educational program for nurses in the intervention group will be addressed.

The sessions will include nursing interventions aimed at improving participants’ knowledge, skills, and attitudes regarding their functional ability, fall prevention measures, anxiety management, and ability to cope with FOF and falls.

The activities to be performed during the intervention were drawn from standardized nursing interventions listed in the Nursing Interventions Classification (NIC) following a review of effective interventions addressing these issues [3,4,9,18,33]:NIC 1665. Functional ability enhancement.NIC 5612. Teaching: prescribed exercise.NIC 6490. Fall prevention.NIC 6486. Environmental management: safety.NIC 4700. Cognitive restructuring.NIC 5820. Anxiety reduction.NIC 5230. Coping enhancement.

To monitor the degree of compliance with the interventions as instructed in the protocol, ad hoc questionnaires will be sent after each session to all the professionals and patients who carry out the intervention in order to assess acceptability, feasibility, and satisfaction.

Health education workshops are a fundamental tool for teaching health education in the primary care setting. This workshop was designed following the methodology recommended by the Madrid Primary Care Management Board and is being reviewed by the Validation Commission for Educational Projects of the Community of Madrid (COVAM) for its free distribution throughout the Autonomous Community of Madrid.

